**5.0 Sample size**

A total of 50 old, active men will be recruited; participants will be separated into 2 groups of 25 and each group will receive either SUPP or PLB. Previous studies have shown that supplementation with creatine monohydrate during RE training in older adults can increase dynamic strength by approximately 1.75 – 3.25 kg more than RE training alone. Using this effect size and a standard deviation of 1.5 kg, n = 20 subjects are needed to detect a difference with α = 0.05 and β = 0.8 using a two-way ANOVA. To account for the possibility of increased variability in the sample set and allowing for a potential 20% dropout rate, a conservative number of 25 subjects per group was chosen.

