**4.0 Population under study**

For this study, we will recruit 50 sedentary yet healthy men aged 70 years or older (n=25 per group). Participants will be considered sedentary if they have not participated in a structured resistance or aerobic training program in the past 6 months. In addition, participants will have a BMI in the normal or overweight range (18.5 – 30.0 kg/m^2^), will have been weight stable for the past 6 months, and will present with a normal resting blood pressure or stage I hypertension at screening (SBP < 140 – 159 mmHg; DBP < 90 – 99 mmHg).

The following exclusion criteria exist to ensure the safety of participants and that certain outcome measures are not confounded:

- Smoking
- Use of simvastatin or atorvastatin
- Use of non-steroidal anti-inflammatory drugs
- Injuries that prevent safe participation in an exercise program
- Prescription blood-thinners
- Diabetes or other metabolic disorders
- Cardiac or gastro-intestinal problems
- Infectious disease or cancer

*4.1 Screening*

A variety of questionnaires and physiological tests will be used to assess eligibility for the study:

Medical Screening Questionnaire and Physical Activity Readiness Questionnaire (PAR-Q): Members of the research team will help potential participants complete a health questionnaire, which will assess the potential participant’s age, physical activity levels, and any medications and medical conditions that the individual may have. We will also measure height and weight. Potential participants must answer ‘no’ to all questions on the PARQ.

OGTT: Potential participants will also undergo a 2 hour 75g OGTT to determine whether they are diabetic (fasting blood glucose > 7.0 mM; 2 hour blood glucose > 11.1 mM) or display impaired glucose tolerance (fasting blood glucose > 5.6 mM; 2 hour blood glucose > 7.8 mM). Details of the OGTT protocol are described below.

Blood pressure: Systolic and diastolic blood pressure must be within the range indicated above in order for an individual to participate in this study. Participants will quietly rest in the supine position for 5 min before measurements are made using an automatic blood pressure cuff. A total of 3 measurements will be made, and the average will be used to assess resting blood pressure.

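### The sample-size paragraph is wrong as written and cannot be reproduced: β = 0.8 means 20% power, and n = 20 does not follow from the stated effect and SD on the natural per-group reading

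*Protocol*

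**What the plan says.** Section 5.0 (Sample size) of the protocol takes its effect from earlier creatine studies in older adults, which it says "can increase dynamic strength by approximately 1.75 – 3.25 kg more than RE training alone". The requirement it derives is that, with "a standard deviation of 1.5 kg, n = 20 subjects are needed to detect a difference with α = 0.05 and β = 0.8"; the method it names is a two-way ANOVA. The final figure of 25 per group is justified by two allowances at once: "To account for the possibility of increased variability in the sample set and allowing for a potential 20% dropout rate".

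Section 9.0 (Data analysis) plans a two-way ANOVA with group as the between factor and time as the within factor, at α of 0.05. Section 7.1 lists six 1RM tests and names none of them as the one behind the calculation. Section 2.0 puts strength, physical function and body composition together in the primary objective.

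The population is described in two ways. Section 5.0 says "A total of 50 old, active men will be recruited", while Section 4.0 says "we will recruit 50 sedentary yet healthy men aged 70 years or older (n=25 per group" and defines sedentary by the absence of structured training in the previous six months.

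**The concern.** A sample-size statement should let a reader put the stated inputs into the stated method and obtain the stated n. Here that cannot be done. The type II error is misstated. The paragraph does not say whether 20 is per group or a total, whether the test is one- or two-sided, which value in the effect range was used, whether 1.5 kg is the SD of change or of a single measurement, or what within-subject correlation the group-by-time ANOVA assumes. The kg figures are not tied to a lift.

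This paragraph is the protocol's only account of what the trial can detect. A reader of the results, particularly of a null strength result, will use it to judge how informative the trial was. An SAP could add detail, but it would not cure figures that the protocol itself states wrongly.

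**Working it through.** **Inputs (all from Section 5.0).** Difference 1.75 to 3.25 kg (midpoint 2.5 kg); SD 1.5 kg; α = 0.05; stated n = 20; dropout 20%; final 25 per group. Assumed, because the protocol is silent: a two-sample comparison of strength gains, two-sided, with 1.5 kg as the SD of the gain. Alternatives are tried in steps 3 and 5.

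**1. The β statement.** Power = 1 − β = 1 − 0.8 = 0.20. Designing for 20% power (two-sided) would need only 2 to 4 per group across the quoted effects. Nobody planned that, so power 0.80 (β = 0.20) is what was meant.

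**2. Reading n = 20 as per group.** This is the natural reading, because 20/(1 − 0.20) = 25 exactly. The normal approximation is n per group = 2(1.960 + 0.842)² × SD²/difference²; the exact figures use the noncentral t.

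| Difference | Standardised effect | n per group, normal approximation | n per group, noncentral t | Power with 20 per group |
|---|---|---|---|---|
| 1.75 kg | 1.75/1.5 = 1.17 | 12 | 13 | 94.9% |
| 2.5 kg | 2.5/1.5 = 1.67 | 6 | 7 | 99.9% |
| 3.25 kg | 3.25/1.5 = 2.17 | 4 | 5 | over 99.9% |

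So 5 to 13 per group are needed for 80% power. Twenty per group is not the answer to the stated question; it is nearer to a 95%-power calculation at 1.75 kg (20 by the normal approximation, 21 by the t).

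**3. Reading n = 20 as a total (10 per group).**
- Two-sided power at 1.75 kg is 69.4%. Eighty per cent power is reached only from 1.325 × 1.5 = 1.99 kg, which lies inside the quoted range.
- One-sided power at 1.75 kg is 80.6%.
- Dropout then gives 10/0.8 = 12.5, so 13 per group. The step to 25 is unexplained.

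**4. The two allowances.** On the per-group reading, 20% dropout takes 20 to 25 and uses the whole increase, so that step contains no separate margin for variability. The real margin lies elsewhere, between the 13 per group needed and the 20 completers expected. With 20 per group, 80% power needs a standardised difference of 0.909, so at 1.75 kg the largest tolerable SD is 1.75/0.909 = 1.92 kg. That is 28% above 1.5 kg (1.92/1.5 = 1.28).

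**5. If 1.5 kg is a single-measurement SD.** The SD of change is then 1.5 × √(2(1 − ρ)), where ρ is the pre-post correlation. At 1.75 kg and 80% power, two-sided, this needs 25 per group at ρ = 0, 20 at ρ = 0.2, 19 at ρ = 0.25 and 13 at ρ = 0.5. The protocol gives no ρ, so these values are illustrative.

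**6. What 50 men deliver.** Detectable difference at 80% power, two-sided: 0.91 SD with 20 completers per group and 0.81 SD with 25. At SD 1.5 kg these are 0.909 × 1.5 = 1.36 kg and 0.809 × 1.5 = 1.21 kg.

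**The case against.** The strongest reply is that 20 can be reached within the gaps the paragraph leaves. Five to 13 per group is 10 to 26 in total, and 20 lies inside that range. A one-sided test at 1.75 kg gives 10 per group, and a single-measurement SD with a correlation near 0.2 gives 20 per group. This stands, and it rules out saying that no reading yields 20. But each route adds something the protocol does not state, and the total reading leaves the step to 25 per group unexplained. The defect is that the figure cannot be reproduced.

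A second reply is that β = 0.8 is only a slip of notation with no effect on N. That is fair as to consequence, but the text still needs correcting.

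Three stronger readings are tempting and are not supported:

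- *The trial is underpowered, or cannot detect the effect it names.* On the stated inputs it is larger than needed. Power falls below 80% at 1.75 kg only if the SD exceeds about 1.92 kg, and at 3.25 kg only above 3.25/0.909, or about 3.57 kg. For assumed SDs of 3, 5 and 10 kg, power across the quoted effects with 20 per group would be 44–92%, 19–52% and 8–17%, but no document gives such SDs.
- *There is no room for extra variability at all.* That is true only of the step from 20 to 25 per group. Measured against the 13 needed at 1.75 kg, there is a margin.
- *The SD was taken from the width of the effect range*, since 3.25 − 1.75 = 1.50. This may be coincidence. The protocol does not say where the SD came from, so the match proves nothing.

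**Conclusion.** The point holds as a failure of justification and not as a shortage of participants. β = 0.8 is wrong as written. On the per-group reading, 20 exceeds the 5 to 13 that the inputs require and gives about 95% power at 1.75 kg, not 80%. On the total reading, two-sided power at 1.75 kg is 69% and dropout does not lead to 25 per group. With 20 per group, the claimed variability allowance is absent from the step to 25; the actual margin is an SD of up to about 1.92 kg at 1.75 kg.

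These figures assume a two-sample t comparison of gains at 0.05, two-sided unless stated otherwise, with 1.5 kg as the SD of the gain. The discrepancy makes the trial larger than its inputs demand, so the point is moderate: worth correcting because this is the only power statement, but no reason to change enrolment. Active in Section 5.0 against sedentary in Section 4.0 is a real contradiction, but a matter of wording.

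**What to change.** Keep N = 50 and rewrite Section 5.0:

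1. Write power = 0.80 (β = 0.20).
2. Say whether n = 20 is per group or a total, and whether the test is one- or two-sided.
3. Choose one design effect from the range, and name the 1RM test it refers to.
4. Say whether 1.5 kg is the SD of change or of a single measurement, give its basis, and state any within-subject correlation used.
5. Restate what 50 men deliver: a detectable difference of 0.91 SD with 20 completers per group and 0.81 SD with 25 (80% power, two-sided 0.05), and 80% power at 1.75 kg up to an SD of about 1.92 kg with 20 completers per group.
6. Express the variability allowance as that SD margin, or delete it.
7. Make the description of the men agree with Section 4.0.

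The cost is one paragraph. The stated justification becomes slightly less favourable, because it will show how far it depends on the SD. Enrolment does not change.

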**6.0 Design**

The overall study design is depicted in Figure 1, below. Participants will be placed in either the SUPP or PLB group, depending on their strength, fat-free mass and body mass index.

[figure not shown]

**Figure 1**. Study schematic. D_2_O, deuterium oxide; 1RM, 1 repetition maximum; VO_2peak_, peak oxygen consumption; OGTT, oral glucose tolerance test; QOL, quality of life assessment, PA, physical activity

*6.1 Assessments*

Approximately 1 week prior to beginning the study, participants will receive a muscle biopsy from *vastus lateralis*, exercise and physical function testing, body composition analysis, an OGTT, and an executive function and quality of life assessment (see Figure 1). These tests will take place over the course of 3-5 days during the same week. During the week these assessments are taking place, participants will complete a 3-day food diary and physical activity log at home, as well as wear an accelerometer (mounted on an arm band) to estimate daily caloric intake, macronutrient distribution and energy expenditure. We will assess glomerular filtration rate (GFR), an estimate of kidney function, by examining cystatin C concentrations in blood samples collected during pre, mid and post-study testing periods.

These assessments will be repeated during week 7, and again upon completion of the study during week 19. Exercise tests (1RM and VO_2peak_) will be repeated at weeks 11 and 15 to ensure an adequate exercise stimulus is maintained during training. The assessments at week 7 and week 19 include serial muscle biopsies for the measurement of the acute satellite cell response to exercise. Details of the serial muscle biopsy protocol are described below. Participants will be asked to refrain from strenuous exercise, caffeine and alcohol for 48 hours prior to each assessment.

*6.2 Phase 1*

Phase 1 of the study is 6 weeks in duration and will be completed primarily at home. Participants will consume 2 study beverages per day – the first approximately 1 hour after breakfast, and the second before bed. Participants will be encouraged to maintain their normal diets and levels of physical activity. We will provide participants with all their study beverages at the beginning of the study.

*6.3 Phase 2*

During Phase 2, participants will perform 3 exercise sessions per week for 12 weeks, while continuing to consume 2 study beverages per day. On non-exercise days, they will consume their beverages exactly as they did in Phase 1: the first 1 hour after breakfast and the second before bed. However on days when they visit McMaster University to exercise, participants’ first study drink of the day will be provided to them upon completion of the exercise session. The second study drink will be taken before bed, as usual.

*6.4 Exercise training*

Exercise training will take place three times per week for 12 weeks. One session per week will consist of HIIT on a bicycle ergometer, and 2 sessions per week will consist of whole body RE. Before beginning a HIIT session, participants will warm up on the bicycle ergometer for 5 min at a low resistance. The exercise will consist of 10 bouts of 60s where participants will sprint (ie. maintain a cadence of at least 90 rpm) at a power predetermined to elicit 90% HR_max_. These bouts will be interspersed with 60s of ‘rest’, where participants will peddle at ~25W at a minimum cadence of 60 rpm. Participants will wear a HR monitor during each session to ensure they are exercise at a safe, appropriate intensity. All HIIT sessions will be followed by a 5 min cool-down at ~25W.

During each whole body RE exercise session, participants will complete 2 upper body and 2 lower body exercises. Leg extension and leg press will be completed during every session, however the upper body exercises will alternate between chest press/horizontal row and shoulder press/biceps curl. For each exercise, participants will complete 3 sets of 8-12 repetitions at 80% 1RM, with the last set completed to failure. Each exercise session will be supervised by a member of the research team.

*6.5 Acute exercise protocol*

To assess the integrated MPS and acute satellite cell response to SUPP in the untrained and trained state, a set of 3 muscle biopsies (1 per day for 3 days) will be conducted at weeks 7 and 19. Immediately prior to participants’ first exercise session in week 7, a muscle biopsy will be taken (time-point: 0 hours). Biopsies will be taken again at 24 and 48 hours post-exercise. This process will be repeated ~1 week following participants’ last exercise session in week 19. Approximately ~ 8 mL of blood will be drawn from an antecubital vein after each biopsy is taken.

*6.6 Deuterated water protocol*

Immediately after the 0 hour muscle biopsies at weeks 7 and 19, but before completing their exercise session, participants will consume a bolus dose of D_2_O (150 mL). Saliva samples will be taken in the morning each day that the participant receives a muscle biopsy. These saliva samples can be taken by participants at home using a simple salivette, and must be taken prior to eating, brushing teeth and consuming D_2_O.

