**2.0 Objectives**

This study will examine the effects of a 12 week RE + HIIT exercise training program combined with multi-ingredient protein-based supplementation (SUPP), compared to 12 weeks of training combined with placebo (PLB), in older men. The substantive objectives of this study are to determine:

1. Primarily, whether the supplement is able to enhance exercise-mediated changes in muscle strength, physical function and body composition.
2. The acute satellite cell response to a single bout of HIIT + RE following 12 wks of protein or placebo supplementation.
3. The effect of each intervention on:
   1. Glucose metabolism and fasting serum lipids.
   2. Cognitive and executive function
   3. Renal function.

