**9.0 Data analysis**

Data will be analyzed using a 2-way analysis of variance (ANOVA) with between (SUPP, PLB) and within (time) group comparisons. Tukey’s HSD post hoc testing will be used to assess differences between the means when interactions are detected. Statistical significance will be accepted at α<0.05.

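### The only visible allocation rule places men in SUPP or PLB by baseline strength, fat-free mass and BMI, with no chance element or concealment stated

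*Protocol*

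**What the plan says.** Protocol section 6.0 (Design) sets the rule: "Participants will be placed in either the SUPP or PLB group, depending on their strength, fat-free mass and body mass index". No other visible section describes how a man reaches his arm. Section 5.0 (Sample size) says that "participants will be separated into 2 groups of 25 and each group will receive either SUPP or PLB", which fixes the group sizes but not the method. Section 4.0 repeats 25 per group.

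The main question in section 2.0 is causal: "Primarily, whether the supplement is able to enhance exercise-mediated changes in muscle strength, physical function and body composition". The comparator is a concurrent placebo arm on the same training. Section 9.0 gives the analysis: "Data will be analyzed using a 2-way analysis of variance (ANOVA) with between (SUPP, PLB) and within (time) group comparisons". It names no term for the three placement variables.

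**The concern.** A rule that makes the arm depend on a man's own baseline values, with no stated role for chance, does not describe random allocation. The SUPP-versus-PLB contrast carries the main objective. If the groups are formed by matching or judgement, factors nobody measured can differ systematically between them: motivation, diet, general health, expected response to training. Several main outcomes (1RM, chair stand, 6-minute walk) depend on effort, so motivation is a plausible prognostic factor.

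At stake is how securely a difference in change between arms can be credited to the supplement, and what the ANOVA p-value refers to. How participants are assigned is a core design element that the protocol itself has to fix. A statistical analysis plan can take account of the allocation, but it cannot add chance or concealment afterwards.

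**Working it through.** **Reading the text.** The protocol states no figure on this point, so the main check is a comparison of its sections.

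| Section | What it contributes on allocation |
|---|---|
| 2.0 Objectives | Two arms, placebo comparator; no method |
| 4.0 Population | 25 per group; no method |
| 5.0 Sample size | Two groups of 25; no method |
| 6.0 Design | Placement depends on strength, fat-free mass and BMI; no chance element, no concealment, nobody named as allocator |
| 9.0 Data analysis | Group-by-time ANOVA; no placement variable named |
| 10.0 Recruitment | Advertising and consent; nothing on assignment |
| 11.0 References | The only visible use of the word *randomized*, in the title of a cited omega-3 study |

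**Timing.** Section 6.1 puts strength and body-composition testing about 1 week before the study begins, and the beverages start with Phase 1 (section 6.2). A rule that uses strength and fat-free mass must therefore be applied once those results exist. Both variables also belong to the main outcome domains in section 2.0. The protocol does not say who assigns, or what that person knows of earlier assignments.

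**What balancing would achieve.** If the sentence means balancing, the arms should be similar on the three variables and, in part, on whatever correlates with them. Nothing follows for factors unrelated to them.

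**Illustration of what a hidden imbalance would do.** The inputs are:
- From section 5.0: 25 per arm recruited; 20% dropout, so 25 × (1 − 0.20) = 20 completers per arm; α = 0.05; SD 1.5 kg.
- Assumed: a two-sided test, because section 5.0 does not state sidedness.
- Assumed: an inert supplement, and a hidden imbalance *d* in mean change, in SD units, of 0.2, 0.3 or 0.5. The documents give no value for *d*.
- Assumed: a two-sample t-test on change, as a simple stand-in for the group-by-time comparison.

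The noncentrality is λ = *d* × √(n/2). The rejection rate is P(|T| > t₀.₉₇₅) for a noncentral t with 2n − 2 degrees of freedom.

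| *d* | in kg (*d* × 1.5) | λ, n = 20 | Rejection, n = 20 (df 38, critical value 2.024) | λ, n = 25 | Rejection, n = 25 (df 48, critical value 2.011) |
|---|---|---|---|---|---|
| 0.2 | 0.30 | 0.632 | 9.5% | 0.707 | 10.7% |
| 0.3 | 0.45 | 0.949 | 15.2% | 1.061 | 18.0% |
| 0.5 | 0.75 | 1.581 | 33.8% | 1.768 | 41.0% |

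All three shifts lie below 1.75 kg, the lower end of the planning effect in section 5.0. For a fixed bias the rate rises with n, so recruiting more men would not help.

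**The case against.** The strongest reply is that the protocol never says assignment is non-random. It names the variables that inform placement and leaves the mechanism open. Stratified randomisation, matched-pair randomisation or minimisation could each be meant by such a loose sentence. The title page was removed and Figure 1, which depicts the overall design, is not shown, so either might use the word *randomised*. This stands. A reader might infer that the trial is definitely non-randomised, or that stronger men are steered to one arm, and the documents support neither inference. The sentence would still need rewriting, because as it stands it makes the arm depend on baseline values and states no chance element.

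A second reply is that the rejection rates rest on assumed shifts and would be the same in any trial with such a bias. This also stands. They show how sensitive the test would be, not that bias exists here.

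A third is that two stronger readings go too far. One is that staff who see the baseline data can foresee or choose the arm. The protocol does not say who allocates, and a balancing rule cannot be foreseen from one man's values alone. The other is that no difference could be attributed to the supplement. A concurrent placebo arm, the same supervised training and a comparison of change over time all weaken some rival explanations. They do not replace randomisation, so what remains is that attribution is less secure.

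Finally, the section 5.0 wording adds little, since random assignment also separates men into groups.

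**Conclusion.** The concern holds in a limited form. The one visible allocation rule makes the arm depend on three baseline variables, and the shown text states neither a chance element nor concealment. Followed as written, it leaves the main contrast open to selection on unmeasured factors and gives the ANOVA no randomisation basis. This holds even on the charitable reading that the groups are to be balanced.

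The size and direction of any bias cannot be derived from the documents. The rates of about 9%, 15% and 34% are illustrative only and depend entirely on the assumed imbalances. The conclusion is also conditional on the parts of the protocol that are not visible.

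The point should be settled before the first man is assigned, because later adjustment can address measured factors only.

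**What to change.** Replace the placement sentence in section 6.0 with concealed, computer-generated 1:1 randomisation that balances on strength, fat-free mass and BMI. Stratified randomisation, matched-pair randomisation, or minimisation with a random element would each serve. With 50 men, cutting each of the three variables in two gives 2 × 2 × 2 = 8 strata, or 50/8 ≈ 6 men per stratum. Minimisation may therefore be easier to run than full stratification, while matched pairs require both members' baseline results before either is assigned. State who generates and holds the sequence and when assignment is released.

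Include the balancing factors in the analysis, through section 9.0 or the statistical analysis plan.

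If assignment is in fact not random, describe the study as non-randomised and limit the causal conclusions accordingly.

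The cost is a rewritten passage and a randomisation list kept by someone who does not enrol participants. No extra participants or procedures are needed, and the balance sought on the three variables is kept. Blinding and the labelling of the beverages are a separate point.

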**7.0 Measurements**

*7.1 Strength and aerobic fitness*

Muscle strength will be assessed using 1 repetition maximum (1RM) testing of the following exercises: leg extension, leg press, chest press, horizontal row, lat pulldown and shoulder press. A 1RM test measures the maximum amount of weight someone can lift for a single repetition, while maintaining good technique. Aerobic fitness (VO_2peak_) will be measured using a graded, maximal exercise test on a bicycle ergometer. Briefly, participants will wear a facemask and begin peddling at ~50-70 rpm at a low resistance. The resistance will gradually increase until participants are no longer able to maintain a cadence of 50 rpm or until they request to stop.

*7.2 Physical function*

The short physical performance battery (SPPB) tests, along with grip strength and a 6 min walk test, will be used to assess physical function. The SPPB tests include a repeated chair stand test (time it takes for participants to stand up from a chair 5 times), a balance test and 8 feet walk test. The scoring system for the SPPB is standardized and will allow us to compare our results to the literature.

*7.3 Body composition*

FM, FFM and bone mineral density will be measured using dual-energy x-ray absorptiometry (DXA), and muscle thickness of the quadriceps muscle will be determined using ultrasound. Waist circumference will be measured using a tape measure at the top of the iliac crest.

*7.4 Satellite cell response*

Muscle cross-sections will be mounted onto glass slides and histochemically analyzed for the following markers of satellite cell activity: Pax7, MyoD, myogenin, myostatin, IL-6, GDF11.

*7.5 Muscle protein synthesis*

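### The week 11 and 15 strength and VO2peak tests have no stated role in the analysis, and the planned ANOVA, in its classical form, drops any man who misses a visit

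*Protocol*

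**What the plan says.** Section 6.1 describes two kinds of visit. The full battery is done before the study; then "These assessments will be repeated during week 7, and again upon completion of the study during week 19". Separately, the 1RM and VO2peak tests "will be repeated at weeks 11 and 15 to ensure an adequate exercise stimulus is maintained during training".

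Section 7.1 makes 1RM the strength outcome: "Muscle strength will be assessed using 1 repetition maximum (1RM) testing of the following exercises". Strength is part of the primary objective in section 2.0. Section 6.5 places the first exercise session in week 7, after that session's baseline biopsy, so week 7 marks the start of training. Weeks 11 and 15 are therefore the only strength measurements between the start and the end of training.

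Section 9.0 states the method: "Data will be analyzed using a 2-way analysis of variance (ANOVA) with between (SUPP, PLB) and within (time) group comparisons". It does not list the levels of time. Section 5.0 arrives at 25 per group by "allowing for a potential 20% dropout rate".

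**The concern.** Two statements fit badly together. The plan expects one man in five to leave, yet it names a method that, as usually computed, needs every visit from every man it includes. It also schedules two extra measurements of a primary-domain outcome during training and mentions them only as a means of keeping the training load adequate.

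A man tested at week 11, or at weeks 11 and 15, who then leaves has shown whether he was gaining strength like the others. If his values are not used, the supplement comparison rests on men who finished. That is a fair comparison only if leaving is unrelated to progress. Precision is also at stake, but less so.

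**Working it through.** **The plan's own figure.** The dropout step reproduces: 20 / (1 − 0.20) = 25 per group, so 5 men per group may be lost. Whether 20 is the right starting number is a separate matter.

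**Assumptions, none of them in the protocol.** Equal variance σ² at each visit. Correlation ρ of 0.7 to 0.9, either the same between any two visits (exchangeable) or per four weeks and decaying with distance (serial). Losses spread evenly over training: 5/3 men per group after each of weeks 7, 11 and 15. Numbers seen per group are then 25, 23.33, 21.67 and 20 at weeks 7, 11, 15 and 19. About 3.3 of the 5 leavers have some training-phase strength data and 1.7 have both visits; the rest have none.

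**Method.** With visit as a category and monotone dropout, the variance of the estimated change can be built up visit by visit, each visit regressed on the earlier ones. All variances below are per group, in units of σ²; doubling for two groups does not alter the ratios.

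*Serial, ρ = 0.8 (week 7 to 19 correlation 0.8³ = 0.512)*

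- Completers at weeks 7 and 19: 2(1 − 0.512)/20 = 0.0488.
- Mixed model on weeks 7, 11, 15, 19: (1 − ρ²)[1/20 + ρ²/21.67 + ρ⁴/23.33] + (1 − ρ³)²/25 = 0.36 × 0.09709 + 0.2381/25 = 0.0445. Ratio to completers 0.911.
- Mixed model without weeks 11 and 15: (1 − 0.512²)/20 + (1 − 0.512)²/25 = 0.0464. Ratio 0.0445/0.0464 = 0.958. A pre-study visit changes neither figure under this structure.

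*Exchangeable, ρ = 0.8*

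- Completers: 2(1 − 0.8)/20 = 0.0200.
- Mixed model on weeks 7 to 19: residual variances at weeks 19, 15 and 11 are 0.2615, 0.2889 and 0.36, with weights 1, 0.3077 and 0.4444, and week 7 has weight −0.2. This gives 0.2615/20 + 0.3077² × 0.2889/21.67 + 0.4444² × 0.36/23.33 + 0.2²/25 = 0.0190. Ratio 0.949.
- Adding the pre-study visit: 0.2471/20 + 0.2353² × 0.2615/21.67 + 0.3077² × 0.2889/23.33 + 0.1111/25 = 0.01864. Ratio to completers 0.932.
- Mixed model on pre-study, week 7 and week 19 only: 0.2889/20 + 0.1111/25 = 0.01889. Ratio 0.01864/0.01889 = 0.987.

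The same calculation at the other correlations gives these variance ratios for the week 7 to 19 difference:

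| Structure | ρ | Weeks 7–19 model vs completers | Five-visit model vs completers | Five-visit model vs mixed model on pre-study, 7, 19 |
|---|---|---|---|---|
| Exchangeable | 0.7 | 0.945 | 0.930 | 0.988 |
| Exchangeable | 0.8 | 0.949 | 0.932 | 0.987 |
| Exchangeable | 0.9 | 0.954 | 0.933 | 0.985 |
| Serial | 0.7 | 0.906 | 0.906 | 0.970 |
| Serial | 0.8 | 0.911 | 0.911 | 0.958 |
| Serial | 0.9 | 0.918 | 0.918 | 0.944 |

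The reduction is about 5 to 9% against completers and about 1 to 6% against a mixed model without weeks 11 and 15. With the pre-study visit in the model, the exchangeable figure against completers is about 7%. With no dropout every category-model ratio is 1. If all leavers go before week 11, the two extra visits add nothing to a mixed model that lacks them.

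**Power.** Taking section 5.0's 1.75 kg and SD of 1.5 kg, 20 per group and a two-sided 0.05 test: z = 1.75 / (1.5 × √(2/20)) = 3.69, and power is Φ(3.69 − 1.96) = 95.8%. Cutting the variance by 5% or 9% gives z = 3.79 or 3.87 and power of 96.6% or 97.2%.

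**The case against.** The strongest reply is that section 6.1 explains why the tests are scheduled, not what may be done with the results. Section 9.0 leaves the time levels open, and visit selection and missing-data handling often belong in a statistical analysis plan, which is not shown here. That stands against one inference a reader might draw: that the protocol discards the week 11 and 15 results, or confines strength to weeks 7 and 19. No sentence says so. It does not answer the rest, because section 9.0 does commit to a two-way ANOVA. Simply adding the two visits as levels would not help: a classical analysis would then need all five visits from each man, and the interaction would have 4 degrees of freedom where three visits give 2. Under the stated method, leaving the visits out is defensible, so the method has to change with the visits.

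A reader might also infer a variance saving of about 14%. That needs exchangeable errors and a straight-line gain over weeks 7 to 19. Most of it comes from the line: with 20 completers and no leavers, imposing linearity alone gives a ratio of 0.90. The protocol supports no such assumption.

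Nor can a worthwhile power gain be claimed on the protocol's own effect sizes, since power at 1.75 kg is already about 96%. And the extra visits do not supply training-phase data on every leaver, since men who go before week 11 have none.

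Finally, comparability is not assured. Weeks 11 and 15 fall within training, while the week 19 acute testing comes about a week after the last session. It is also a matter of reading whether the 48-hour restriction before assessments covers the interim tests. This favours visit as a category over a slope.

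**Conclusion.** The point holds as a minor improvement. The protocol gives the week 11 and 15 tests no stated analytic role, and it names a method that in its classical form excludes incomplete men while planning for 20% of them. The main benefit of changing this is less reliance on completers, because training-phase data from men who leave after week 11 would count. The precision gain is secondary: about 5 to 9% of variance against completers, about 1 to 6% against a mixed model without these visits, and none without dropout. Those figures depend on assumed correlations of 0.7 to 0.9 and on dropout spread evenly over training. At the protocol's 1.75 kg the power gain is about 1 percentage point.

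**What to change.** In sections 6.1 and 9.0, name the week 11 and 15 1RM and VO2peak values as outcome data, in addition to their use in training. For strength and VO2peak, replace the ANOVA with a likelihood-based mixed model on all available visits (pre-study, weeks 7, 11, 15 and 19), with visit as a category and group-by-visit terms.

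Report the SUPP minus PLB difference in change to week 19 both from pre-study and from week 7. Both are needed: week 7 follows six weeks of supplement, and Hypothesis 1 expects an independent supplement effect on strength, which a contrast from week 7 alone would remove. A linear-slope model over weeks 7 to 19 can serve as a sensitivity analysis.

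The cost is a change of wording and slightly more analysis work, with no added testing. The model relies on data being missing at random, which should be stated.
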